### Data collection

2.6

All data will be gathered from electronic medical record. All consecutive patients operated on for urgent digestive surgery during the study period will be screened and included if they fulfil the inclusion criteria.

Demographic characteristics, comorbidities, clinical and analytical variables, SARS-CoV-2 infectious status (pre- and post-operative periods), clinical diagnosis, intraoperative findings and postoperative course (30-day morbidity, 30-day reinterventions, hospital stay, 30-day readmissions, and mortality at 30 and 90 days) will be recorded (Supplementary data file 2).^[25,35]^

All values necessary for the automatic calculation of the surgical prognostic scores shall also be included (Table 5).^[39,45]^

Prognostic factors recently described in COVID-19-positive patients will also be recorded: advanced age, hypertension, smoking, diabetes, chronic obstructive pulmonary disease (COPD), cardiovascular history, lymphocyte and platelet count, alanine-aminotransferase (ALT), C-reactive protein (CRP), D-dimer, ferritin, procalcitonin (PCT), lactate-dehydrogenase (LDH), troponin, prothrombin time, “neutrophil-to-lymphocyte ratio” (NLR) and “platelet-to-lymphocyte ratio” (PLR).^[8,11,16,26,35,49,50,60–64]^

Among postoperative complications, those currently considered “characteristics” of COVID-19 (pneumonia, respiratory failure, venous thromboembolism, acute myocardial infarction, cerebrovascular accident, peripheral arterial ischemia, intestinal ischemia, cardiomyopathy, or pericarditis) will be analyzed in depth.^[8,35,58]^

An electronic Case Report Form (eCRF), based on REDCap platform *(Research Electronic Data Capture software, REDCap Consortium)*, has been created *ad hoc* for this study (Supplementary data file 3).^[65]^

### Sample size

2.8

Due to the exploratory nature of our aim, no formal calculation of sample size was performed. It will be defined by the total number of patients who underwent emergency gastrointestinal surgery during the 2 study periods at the participating hospitals. We expect to include more than 2000 patients.

### Statistical analysis

2.9

Baseline characteristics will be described using standard descriptive statistics, and a descriptive and exploratory comparative analysis between both cohorts will be carried out.

The cumulative incidence of mortality (and its 95% confident interval) and the incidence of morbidity (and its 95% confident interval) at 30 and 90 days will be estimated by positive/negative SARS-CoV-2 infection status (cohort A) and in the control group (cohort B).

To minimize the selection bias effect of potential confounders, propensity scores will be estimated using a multinomial model to estimate the probability that subjects were SARS-CoV-2-positive, SARS-CoV-2-negative or control. Subjects will be matched using the propensity scores. After matching, to identify imbalance between groups, the standardized mean difference will be estimated and plotted. In the matched sample, the cumulative incidence of mortality (and its 95% confidence interval) and the incidence of morbidity (and its 95% confidence interval) at 30 and 90 days will be compared using a generalized linear model with a binomial distribution and a logarithm link function. Those variables that remain imbalanced between groups after matching would be added to the model with an adjusting purpose.

A generalized linear model with a binomial distribution and a logarithm link function will be used to estimate relative risk as a measure to indentify prognostic factors associated with 30 and 90 days mortality and morbidity incidences. Five predictive scores of postoperative morbidity and/or mortality will be calculated according with Table 5: POSSUM-mortality, POSSUM-morbidity, P-POSSUM, LUCENTUM-logistic regression, and LUCENTUM-CHAID.^[38,39,42–45]^ Their applicability on postoperative morbidity or mortality prediction in COVID-19 pandemic will be assessed.

Data analysis will be carried out using R version 4.02 or superior (R Core Team, 2019; R: A language and environment for statistical computing. R Foundation for Statistical Computing, Vienna, Austria. URL https://www.R-project.org/).

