These and other questions should be answered as soon as possible. The analysis of real data on urgent gastrointestinal surgery in patients operated on during this period could provide the necessary information.^[36,41]^ However, in order to control the confounding factors of the pandemic scenario, cohort studies should provide additional information on the pathology and clinical condition of patients at the time of urgent surgery, for example with prognostic surgical scores. The classic surgical prognostic scales validated for the estimation of postoperative risk (scores POSSUM-mortality, POSSUM-morbidity, P-POSSUM, LUCENTUM-logistic regression, and LUCENTUM-CHAID) may not be adequate in patients undergoing emergency surgery during the pandemic period.^[38,39,42–45]^ Therefore, it may be necessary to consider other prognostic factors and design a new and specific prediction model for patients infected with SARS-CoV-2.^[46,47]^ Currently, we only have extrapolated prognostic scores for the set of COVID-19-positive patients, with little data on the specific subgroup of surgical patients, and even less information on the postoperative evolution after urgent digestive surgery.^[15,21,22,48–51]^

It would also be advisable to compare a COVID-19-positive group of patients with a simultaneous COVID-19-negative group (both in the “pandemic period”) and with a “pre-pandemic” control group in the same hospitals.

A registry of these characteristics would provide firmer evidence on their clinical profile and would make it possible to adequately estimate patient's postoperative risk.^[46]^ The few studies published to date address these issues superficially, with unadjusted raw data and a low degree of statistical analysis and scientific evidence.^[10,35,52]^

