### Settings

2.2

A total of 30 surgical teams from different Spanish hospitals have been proposed to participate in this study (see Supplementary data file 1), which has been coordinated by the Department of General and Digestive Surgery of the Bellvitge University Hospital (L’Hospitalet de Llobregat, Barcelona, Spain). All hospitals participating are from Spain, with different surgical capabilities.^[55]^

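### Section 2.9 fixes a log-binomial model on a propensity-matched sample without saying how hospital enters, so the infection contrast may carry hospital differences and the crude incidence intervals in the large groups are likely too narrow

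*Protocol article*

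**What the plan says.** Section 2.9 of the protocol article (Statistical analysis) has three relevant steps.

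- **Crude estimates.** Cumulative incidences with 95% intervals are estimated for 2020 positives, 2020 negatives and 2019 controls.
- **Matching.** The article says that "propensity scores will be estimated using a multinomial model to estimate the probability that subjects were SARS-CoV-2-positive, SARS-CoV-2-negative or control", and then "Subjects will be matched using the propensity scores". It does not list the covariates of the score.
- **Comparison.** In the matched sample the incidences "will be compared using a generalized linear model with a binomial distribution and a logarithm link function". A safeguard follows: "Those variables that remain imbalanced between groups after matching would be added to the model with an adjusting purpose". The same model family is used again to look for prognostic factors.

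On the structure of the data, section 2.2 (Settings) states: "A total of 30 surgical teams from different Spanish hospitals have been proposed to participate in this study". It adds that the hospitals differ in surgical capability. The Introduction argues for a pre-pandemic "control group in the same hospitals", and section 2.7 (Data quality) excludes hospitals that do not supply their eligible patients for both periods. All three groups are therefore drawn from the same set of hospitals.

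The article names no hospital term, stratum or random effect, and no variance that allows for hospital or matched set.

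**The concern.** The estimator is not left open: family, link, matching and the rule for residual imbalance are all given. Fitted as named, such a model treats patients as independent and does not separate hospitals.

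That matters here for a reason the article supplies. Its Introduction blames overloaded intensive care and interventional radiology for deaths among complicated patients, infected or not, and its second hypothesis is that hospital collapse raised mortality in the non-infected. If infected patients are found mainly in the hardest-pressed hospitals, a positive-versus-negative comparison that ignores hospital mixes infection with strain. Matching on the score alone may also pair patients across hospitals, which gives up the benefit of same-hospital groups.

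Two lesser issues follow. Intervals for the crude incidences, which express the primary outcome, ignore variation between hospitals. And a log-binomial model can fail to converge, or stop at a fitted risk of 1, once covariates are added, most readily for a common outcome such as morbidity.

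**Working it through.** **Inputs.** From the article: up to 30 hospitals (section 2.2) and more than 2000 patients over both periods (section 2.8). It gives no event rate, infection prevalence, intracluster correlation (ICC) or effect size, so there is no stated figure to reproduce and everything else below is assumed.

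**1. Crude incidences.** Assume 1000 patients per period, so m = 1000/30 = 33.3 per hospital. Design effect DE = 1 + (m − 1) × ICC; the standard error is understated by √DE; actual coverage of a nominal 95% interval = 2Φ(1.96/√DE) − 1.

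| Group | m | ICC | DE | √DE | Coverage |
|---|---|---|---|---|---|
| 2019 controls | 33.3 | 0.01 | 1 + 32.3 × 0.01 = 1.32 | 1.15 | 91% |
| 2019 controls | 33.3 | 0.05 | 1 + 32.3 × 0.05 = 2.62 | 1.62 | 77% |
| 2020 positives | 4 | 0.01 | 1 + 3 × 0.01 = 1.03 | 1.01 | about 95% |
| 2020 positives | 4 | 0.05 | 1 + 3 × 0.05 = 1.15 | 1.07 | about 93% |

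The positive rows assume 12% infected, spread evenly (0.12 × 33.3 = 4 per hospital); clustering of positives in a few hospitals would raise them. The 2020 negatives (0.88 × 33.3 = 29.3 per hospital) have DE = 1.28 to 2.42.

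**2. Group contrasts.** A simulation used 30 hospitals and about 2000 patients, half of them in 2020, with 12% of the 2020 patients infected and 5% baseline mortality. The true relative risk was 2.0 for positive versus negative and 1.0 for negative versus 2019. It compared an unadjusted log-link relative risk, with independence standard error, with a Mantel–Haenszel relative risk stratified by hospital. There were 600 runs per scenario, and propensity matching was not simulated.

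| Hospital prevalence and mortality | Positive vs negative, no hospital | Coverage | Stratified by hospital |
|---|---|---|---|
| Unrelated, or one of them constant | 1.94 to 1.99 | 94% to 96% | 1.93 to 2.02 |
| Correlation 0.5, log-SD of mortality 0.3 | 2.26 | 92% | 2.04 |
| Correlation 0.5, log-SD of mortality 0.5 | 2.42 | 86% | 1.96 |

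In the two correlated rows the logit-SD of prevalence is 1.0. The bias is 2.26/2.0 = +13% and 2.42/2.0 = +21%. It does not shrink with size: the last scenario at 6000 patients (300 runs) gave 2.44 with 71% coverage.

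For negative versus 2019, coverage was 94% to 97% throughout, because period is crossed with hospital. For positive versus negative at 2000 patients, mean model standard errors of 0.276 to 0.325 stood against empirical values of 0.289 to 0.339, a gap of about 5% at most.

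**3. Convergence.** With three continuous covariates and a logistic truth, log-binomial fits failed or reached the boundary in about one in ten to nearly all datasets (n = 300, 35% events), depending on the predictor strength assumed. Log-link Poisson fits converged every time. So wide a range shows that failure is possible; it does not predict a rate for this study.

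**The case against.** The strongest reply is that silence in a condensed article is not a decision. The propensity covariates are not listed, the full variable list is in a supplement that is not shown, and the imbalance rule could bring hospital into the outcome model. This stands as a limit on the claim. A reader might infer that the plan excludes hospital; the article does not say so. But neither route is stated, while the estimator itself is.

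A reader might also infer that all the intervals are wrong. The documents and the check do not support that. The design effect concerns the crude incidences only. For the contrasts the error is small, and ignoring matched sets usually makes intervals too wide rather than too narrow. Even for crude incidences the ICC is assumed. The hospitals were invited rather than sampled at random, so the need to allow for variation between them depends on whether inference reaches beyond them. The article hopes its results will extrapolate to other surgical teams, which suggests that it does.

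Nor is confounding established. It needs hospital to be absent from both models and prevalence to be related to mortality across hospitals. The article makes the second plausible and proves neither.

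On convergence, a matched comparison with the group term alone raises no difficulty. The issue arises only with added covariates and in the prognostic-factor models.

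**Conclusion.** The point holds as a gap in a method that is otherwise fixed, and as a conditional risk. Taken literally, section 2.9 does not protect the positive-versus-negative contrast, the first part of the main hypothesis, from hospital differences that the article itself regards as harmful. The size is about +13% to +21% in the relative risk under the assumed link between prevalence and mortality, and essentially nil without it. The 2020-negative versus 2019 contrast is largely safe.

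Independence intervals for crude incidences in the large groups are likely too narrow by a factor of 1.15 to 1.62 in the standard error for ICC 0.01 to 0.05. In the positive group the effect is slight if cases are evenly spread. Thirty hospitals is an upper figure, since teams were only proposed and section 2.7 may exclude some. Confidence is good on what the article names and moderate on the size of any bias.

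**What to change.** State in section 2.9 how hospital is handled:

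- Include hospital in the propensity model and as a stratum or term in the outcome model, or match within hospital where numbers allow.
- Use calendar time, as week of the year so that it applies to 2019 too, as a covariate. Exact matching on hospital and week would give about 30 × 17 = 510 cells with about 1000/510 ≈ 2 patients each per period, which is too sparse.
- Estimate relative risks by log-link Poisson regression with variance clustered on hospital and a small-sample correction for at most 30 clusters. This also covers matched sets when they lie within one hospital; sets that cross hospitals need separate allowance.
- Use the same clustered variance for the per-group incidences.

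The cost is some added wording and different options in R, with no new data. Intervals will be somewhat wider, and within-hospital matching would leave some patients unmatched. With only about 4 positives per hospital under the assumption above, separate indicators for every hospital may be unstable, so a stratified analysis or a random intercept may be easier to fit.

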1.patients’ fear of visiting the hospital during the pandemic (and/or home confinement) makes that clinicians face with more advanced surgical pathologies in the moment of consultation;2.“saturation” of the health system, collapse of the emergency departments, and the misinterpretation of septic symptoms in this context can easily add an “extra” delay in diagnosis;3.conservative treatment (nonsurgical management) may be forced beyond usual local standards, making patients who ultimately need a surgical rescue worse off;4.work overload of supporting services, such as intensive care units and interventional radiology, may increase “failure to rescue” in complicated patients, not just COVID-19-positive patients.^[16,21–23,32–35]^

Furthermore, we can’t exclude a synergistic negative effect of SARS-CoV-2 infection on the acute disease that prompted surgical consultation.^[35]^

The COVID-19 pandemic seems to directly or indirectly modify the clinical profile of the urgent surgical pathology treated in a General Surgery Emergency Department (epidemiology, surgical indications, clinical severity, diagnostic delay, complications, etc.).^[21,36]^ The surgical indications and operative techniques for urgent digestive surgeries performed during the “pandemic” period may differ from the “pre-pandemic” period, as well as the postoperative complication and mortality rates of COVID-19-negative patients during the pandemic period.^[21,23,25,37]^

Digestive surgeons ask several questions in this particular epidemiological context:

1.To what extent does COVID-19 infection modify the nature, clinical profile, or postoperative evolution of urgent surgical pathology?;^[17,21,26]^2.Does the socio-sanitary context of a pandemic modify the presentation, severity, diagnostic delay, or postoperative evolution of COVID-19-negative patients undergoing emergency surgery?;^[21,32]^3.Do the usual postoperative risk prediction scales maintain their validity in this period or do they require any kind of adjustment based on other specific prognostic criteria?;^[38,39]^4.Is it appropriate to perform emergency surgical interventions with the classic clinical indications or should some acute pathologies be deferred and the surgery be postponed until normal conditions prevail?;^[10,15,25,36,37]^5.Are all the surgical techniques and approaches commonly used in emergency digestive surgery equally safe during COVID-19 pandemic period?^[9,23,33,36,37,40]^

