### Outcomes

2.5

The primary outcome is the cumulative incidence of mortality for any cause at 30 days after urgent gastrointestinal surgery.Secondary outcomes are:

1.Cumulative incidence of all-causes mortality within 90 days after surgery.2.Cumulative incidence of any postoperative morbidity within 30 days after surgery: overall postoperative complications and/or complications specifically associated with the evolution of COVID-19 (Table 2).^[8,58]^3.Cumulative incidence of severe 30 day-postoperative complications, >IIIA grade according to the Clavien-Dindo score (Table 3).^[56,57,59]^4.Failure-to-rescue defined as the percentage of patients dying of any cause as a consequence of any postoperative complication.5.Length of hospital stay (from the day of admission to the date of hospital discharge or death).6.“Physiological” and “operative severity” to calculate the estimated risks of mortality and postoperative complications according to 5 surgical prognostic scales (Table 5): POSSUM-mortality and POSSUM-morbidity scores, P-POSSUM score, LUCENTUM-logistic regression, and LUCENTUM-CHAID scores.^[14,38,39,42–45]^7.Attitude of the surgeons due to the influence of the SARS-CoV-2 pandemic regarding the “moment of surgical intervention”:^[21,22,32,33]^ Did it change? [No/Yes]; if affirmative:-Was the patient probably seen for consultation later than usual (more advanced pathology)?-Was the diagnosis of the surgical pathology delayed?-Was urgent intervention delayed for logistical problems (“hospital” delay)?-Was a conservative/non-operative treatment “over-indicated”?8.Attitude of the surgeons due to the influence of the SARS-CoV-2 pandemic regarding the “surgical technique” used:^[9,10,15,36,37,40]^ Did it change? [No/Yes]; if affirmative:-Was the surgical technique being “more conservative than usual” or “more aggressive than usual”?

**Table 5 T5:** Postoperative prognostic scores.

Score	Equation	Prediction
POSSUM (mortality)	Ln [R/(1–R)] = –7.04 + (0.13 × physiological score) + (0.16 × operative severity score)	Postoperative mortality
POSSUM (morbidity)	Ln [R/(1–R)] = –5.91 + (0.16 × physiological score) + (0.19 × operative severity score)	Postoperative morbidity
P-POSSUM	Ln [R/(1–R)] = –9.065 + (0.1692 × physiological score) + (0.155 × operative severity score)	Postoperative mortality

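### For COVID-19-negative 2020 patients versus 2019 controls, the rule that adjusts for whatever stays imbalanced can take out the part of the pandemic effect that runs through severity at surgery

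*Protocol article*

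**What the plan says.** Section 2.9 (Statistical analysis) fits one multinomial propensity model for three groups: SARS-CoV-2-positive, SARS-CoV-2-negative and 2019 control. It matches on the scores, checks standardized mean differences, and compares mortality and morbidity in the matched sample with a log-link binomial model. It then says: "Those variables that remain imbalanced between groups after matching would be added to the model with an adjusting purpose". It names no covariates for the propensity model. Incidences with 95% confidence intervals are also estimated by group, with matching introduced only afterwards.

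The article gives severity at surgery three roles:

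- **Information for confounding control.** The Introduction says that "in order to control the confounding factors of the pandemic scenario, cohort studies should provide additional information on the pathology and clinical condition of patients", meaning their state when operated on, and gives prognostic surgical scores as the example.
- **Mechanism.** The Introduction lists four ways the pandemic may worsen outcome. Patients' fear of attending hospital "makes that clinicians face with more advanced surgical pathologies in the moment of consultation"; system saturation "can easily add an “extra” delay in diagnosis"; and non-operative treatment may be pushed too far, "making patients who ultimately need a surgical rescue worse off". The fourth, overload of supporting services, "may increase “failure to rescue” in complicated patients, not just COVID-19-positive patients". The Discussion repeats the point about more advanced disease and extends it to uninfected patients.
- **Outcome.** In section 2.5, secondary outcome 6 is physiological and operative severity, used "to calculate the estimated risks of mortality and postoperative complications according to 5 surgical prognostic scales". Secondary outcome 7 asks about later consultation, delayed diagnosis and delayed surgery.

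The second working hypothesis (end of the Introduction) is that hospital collapse in the first wave raised 30-day mortality in uninfected patients. The Discussion says this will be examined by contrasting the COVID-19-negative 2020 subgroup with the 2019 controls.

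**The concern.** A confounder is a cause, or a marker of a cause, of both exposure and outcome. A variable that the exposure changes on its way to the outcome is a mediator, and conditioning on it removes the part of the effect that passes through it. In the 2020-negative versus 2019 contrast the exposure is the pandemic period, and on the article's own account that period makes patients arrive later and sicker.

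The post-matching rule selects variables by imbalance alone. If the second hypothesis is right, severity and delay should differ between the years, so the more the pandemic changed severity, the more likely the rule is to select it. Section 2.9 has no exclusion for variables the exposure can alter. The matched comparison is where the groups are formally compared, so a reader would take its RR as the answer to the second hypothesis, when it may answer a narrower question.

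**Working it through.** The article gives no effect size, significance level or power (section 2.8), so there is no stated figure to reproduce. The illustrations below show direction and possible size only; their inputs are assumed unless marked otherwise.

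**1. Limiting case: the whole effect runs through severity.** Assume mortality of 12% with advanced disease and 2% otherwise in both years, and advanced disease in 20% of patients in 2019 and 35% in 2020.

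- 2019: 0.20 × 0.12 + 0.80 × 0.02 = 0.040
- 2020: 0.35 × 0.12 + 0.65 × 0.02 = 0.055
- Crude RR = 0.055 / 0.040 = 1.375; RR within each severity stratum = 1.00

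**2. With a direct effect as well.** The P-POSSUM mortality equation is taken from Table 5: logit(R) = −9.065 + 0.1692 × physiological score + 0.155 × operative severity score. Assumed: control physiological score 12 + Gamma(shape 2, scale 4); operative severity score 6 + Gamma(shape 2, scale 3). Control mortality is then about 4.3%. The pandemic is assumed to raise the physiological score by 1 to 4 points and to multiply risk at a given severity by a direct RR. Holding severity equal leaves only the direct RR, so the share of the log RR removed is 1 − ln(direct RR) / ln(total RR).

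| Shift (points) | Direct RR 1.0: total RR (removed) | Direct RR 1.2: total RR (removed) | Direct RR 1.5: total RR (removed) |
|---|---|---|---|
| 1 | 1.15 (100%) | 1.37 (42%) | 1.70 (24%) |
| 2 | 1.31 (100%) | 1.57 (60%) | 1.94 (39%) |
| 3 | 1.49 (100%) | 1.79 (69%) | 2.22 (49%) |
| 4 | 1.70 (100%) | 2.04 (74%) | 2.52 (56%) |

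Example: 1 − ln(1.2) / ln(1.37) = 1 − 0.182 / 0.315 = 0.42.

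A simulation with 200,000 patients per group and a 3-point shift, matched on the P-POSSUM linear predictor, agrees. With direct RR 1.0, the unadjusted RR of 1.50 becomes 1.01. With direct RR 1.2, 1.76 becomes 1.18.

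**3. The same crude RR without any harm.** Only operated patients are included (section 2.3), and the Introduction says non-operative treatment may have been extended. Keep the death risks from step 1. Let 2019 have 200 advanced and 800 mild operated patients. Let 2020 have the same 200 advanced but only 371 mild patients reaching surgery (assumed).

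- Advanced share in 2020: 200 / 571 = 35%
- Mortality in 2020: (200 × 0.12 + 371 × 0.02) / 571 = 31.42 / 571 = 5.5%
- Crude RR is about 1.38, although no patient became sicker

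Steps 1 and 3 give the same crude and severity-matched results from different causes. The crude and matched RRs alone cannot tell them apart.

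**The case against.** The strongest objection is that section 2.9 names no covariates. It never says that POSSUM, LUCENTUM, urgency or complexity enter the propensity model. Its only stated use of the scores is to calculate them and assess their predictive value, and Table 4 schedules them at enrollment. The covariate list may sit in a document not shown, and the imbalance rule can be read as covering only variables already chosen for matching. This stands as a limit: the point is conditional on severity being among the variables matched on or checked for balance. It does not dispose of the point, because the Introduction calls for this information to control confounding and the rule as written excludes nothing.

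Second, severity may differ between years because fewer mild cases were operated on, and then adjusting is right. Step 3 of the working shows this can produce the same crude RR. It stands, and it is why neither estimate should be reported alone.

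Third, the second hypothesis speaks of hospital collapse, and part of late presentation comes from patients' fear. One could argue that severity on arrival should be held equal for that part. This is a fair debate about the target of estimation, but it should be settled by a stated choice, not by which variables happen to stay imbalanced.

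A reader might also infer three stronger claims that the article does not support:

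- **That matching erases the pandemic effect.** Failure to rescue and direct viral injury do not run through severity at surgery and would survive adjustment. An RR of 1.00 is the limiting case.
- **That the total difference disappears from the report.** Group incidences before matching are planned and keep it visible, though without confounder control.
- **That severity should be dropped from every comparison.** Among 2020 patients, positive versus negative, severity can be a genuine confounder. Section 2.6 records infection status both before and after surgery, so severity at surgery can precede infection.

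**Conclusion.** The point holds for one contrast and conditionally. For COVID-19-negative 2020 patients versus 2019 controls, the article treats severity and delay as mechanism and outcome, yet frames clinical condition at surgery as confounding information and fixes a rule that can adjust for it. If severity enters by either route, the matched RR no longer estimates the total effect of the pandemic period and, where the pandemic made patients sicker, understates it.

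The size cannot be derived from the article. On the assumed inputs, between 24% and 74% of the log RR is removed when the direct RR is 1.2 to 1.5, and all of it only when there is no direct effect. These figures assume that the shift in severity is caused by the pandemic and not by selection for surgery, which the data may not be able to separate. It deserves correction before analysis because it decides what the matched comparison for the second hypothesis means.

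**What to change.** Set the covariates per contrast before the analysis, and state that imbalance alone does not bring in a variable the pandemic can change.

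- **COVID-19-negative 2020 versus 2019:** report two labelled estimates. The first is matched or adjusted only on characteristics fixed before the acute episode: age, sex, comorbidities, functional status, malignancy and hospital. The second further adjusts for severity, urgency and complexity, and is read as the difference not explained by severity or case-mix at surgery. State that the first may include changes in who was selected for surgery.
- **COVID-19-positive versus COVID-19-negative within 2020:** severity may stay in the adjustment set, because it can be a genuine confounder there.

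The cost is a few sentences of wording and one extra model. No new data are needed: section 2.7 already requires age, sex, functional status, comorbidities, malignancy, urgency and complexity for every analysed patient, and section 2.6 collects the score components. The downside is that case-mix selection remains in the first estimate, so the two must be read together.
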